##### Quantitative data

The quantitative data will be exported to SPSS version 26 (IBM, Chicago, IL, USA) for analysis. Descriptive statistics of the sample and each study measure. Data obtained from the EORTC-QLQ-30 and Hospital Anxiety Depression Scale will be analysed using a paired *t* test (non-parametric, Wilcoxon test). The weekly self-report tracking module will examine adherence to the exercise prescription. Changes in attitudes to physical activity, confidence, and burden will explored post-intervention.

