**Methods:**

Thirty-five individuals diagnosed with lung cancer, or cancer affecting the lung (e.g. pleural mesothelioma), will be recruited into a single-intervention arm. The platform will provide tailored resources and a personalised physical activity programme using IF-THEN algorithms. Exercise prescription will be tailored on factors such as self-reported specific pain location, exercise history, and current physical fitness. In addition, modules grounded in behaviour change will supplement the physical activity programme and will focus on topics such as exercise benefits, safety, goal setting, and tracking. The primary outcome will be assessed using pre-established criteria on feasibility and mixed-methods approach for acceptability.

Secondary outcomes will explore changes in the physical activity, quality of life, anxiety, and depression.

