## Methods

### Study design

This study is a single-group feasibility study. The participants will complete an 8-week web-based computer-tailored physical activity intervention with personalised educational resources. Mixed-methods analyses will be employed with primary outcomes exploring the feasibility and acceptability of the web-based platform. Secondary outcomes examining quality of life, anxiety, and depression will be collected via questionnaires. Physical activity and exercise will be collected weekly via tracking modules, wherein participants can self-report physical activities and exercises completed and any concerns. Fifteen participants will be invited to participate in post-study interviews will be conducted. Interviews will continue if not saturated.

The study has been registered on the ClinicalTrails.gov website [43] (ID: NCT05121259)*,* and ethical clearance was obtained by the Health Research Authority (approval: 21/SC/0174). The reporting of the study protocol adheres to the Standard Protocol Items: Recommendations for Interventional Trials (SPIRIT) guidelines [44]. A participant timeline is presented following the SPIRT guidance in Table 1.

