#### Health-related outcomes

Health-related outcomes will be collected at baseline upon registration to the website and immediately following the completion of week 8. The health-related outcomes being assessed pre- and post-study will be the quality of life, anxiety, and depression. Health-related quality of life will be explored via the 30-item European Organisation for Research and Treatment of Cancer Quality of Life Questionnaire-validated questionnaire (EORTC QLQ-C30; version three) [75]. The quality of life domains are divided into multi-item subscales, functional (e.g. physical, role, cognitive, emotional, and social), symptom scales (e.g. fatigue, pain, nausea/vomiting, and dyspnoea), financial hardship, and global health status.

Anxiety and depression will be measured using the Hospital Anxiety Depression Scale [76]. The Hospital Anxiety Depression Scale will measure anxiety and depression using a 14-item scale (seven items for depression and seven items for anxiety). The Hospital Anxiety Depression Scale has been illustrated to show an excellent screening of those with and without clinical symptoms of depression and anxiety to longer questionnaires (MADRS-S and STAI-S) using web-based platforms for those living with and beyond cancer [77].

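### Before/after significance tests on at least 13 quality-of-life and mood scales in one uncontrolled group carry roughly a 25–50% chance of a spurious significant change; report descriptive changes with confidence intervals instead.

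*Protocol article*

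**What the plan says.** The design is uncontrolled: "This study is a single-group feasibility study" (Study design). The Abstract gives the health outcomes an exploratory role: "Secondary outcomes will explore changes in the physical activity, quality of life, anxiety, and depression".

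Under Health-related outcomes, the EORTC QLQ-C30 and the HADS are collected at baseline and straight after week 8. The QLQ-C30 domains are listed as "functional (e.g. physical, role, cognitive, emotional, and social), symptom scales (e.g. fatigue, pain, nausea/vomiting, and dyspnoea), financial hardship, and global health status". The HADS is a "14-item scale (seven items for depression and seven items for anxiety").

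Under Quantitative data, the article first promises descriptive statistics for the sample and for each measure. It then says: "Data obtained from the EORTC-QLQ-30 and Hospital Anxiety Depression Scale will be analysed using a paired" t "test (non-parametric, Wilcoxon test"). It singles out no scale.

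The Sample size section sets a maximum of 35 participants. It says a formal calculation is unnecessary because success rests on pre-established criteria. Those criteria, under Data analysis, concern recruitment, retention, usability, satisfaction and interview themes. None of them uses the quality-of-life or mood results.

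**The concern.** The protocol declines to size the study for hypothesis testing, then commits to a hypothesis test on every quality-of-life and mood scale. This is a stated method that fits the design badly, rather than a detail left for later.

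There are two separate problems:

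- **Multiplicity.** With a dozen or more tests and no scale singled out, some p-value below 0.05 is fairly likely even if nothing has changed.
- **Attribution.** In a single group followed for 8 weeks, a real change on even one scale may reflect recovery after treatment, regression to the mean or selective drop-out. The multiplicity figure does not measure this problem, and correcting for multiplicity would not remove it.

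What is at stake is how the results are read and reused. The Conclusion plans a later comparison of a digital tool with standard care. That study needs the size of the change, its spread and the baseline/week-8 correlation. A list of p-values supplies none of these and invites a reader to pick out the significant scales.

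**Working it through.** The protocol states no significance level, power or error rate for these tests, so there is no figure of its own to reproduce.

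**Inputs**

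- Scales named under Health-related outcomes: 5 functional + 4 symptom + 1 financial + 1 global = 11, plus 2 HADS scores = 13. The functional and symptom lists are introduced as examples, so 13 is a minimum. Seventeen is used below as an assumed higher count.
- Significance level: not stated. Assumed two-sided 0.05 per test, unadjusted.
- Pairs: maximum 35 (Sample size) and retention target of at least 85% (Pre-established criteria). 0.85 × 35 = 29.75, so about 30. This assumes that those retained also supply week-8 questionnaires. The article defines retention by completion of the intervention, which is not quite the same thing.
- Correlation between change scores: not given. Varied from 0 to 0.7.

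**Step 1: independent scales.** The chance of at least one p < 0.05 with no true change is 1 − 0.95^k.

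- k = 11: 1 − 0.95^11 = 43.1%
- k = 13: 1 − 0.95^13 = 48.7%
- k = 17: 1 − 0.95^17 = 58.2%

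**Step 2: correlated scales.** Simulation with 30 pairs, equicorrelated normal change scores, no true change, a paired t test on every scale and 1,000 runs per setting. The Monte Carlo standard error is about 1.5 percentage points: for example, √(0.322 × 0.678 / 1000) = 0.015.

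| Correlation | 13 scales | 17 scales |
|---|---|---|
| 0 | 49% | 56% |
| 0.3 | 42% | 49% |
| 0.5 | 32% | 39% |
| 0.7 | 26% | 27% |

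**Step 3: expected false positives.** 13 × 0.05 = 0.65. Correlation does not alter this. It only bunches the false positives into fewer studies.

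**Step 4: does the choice between t and Wilcoxon matter?** With 13 scales, letting a Shapiro-Wilk pre-test choose the test gives 50%, 43%, 34% and 26% at the four correlations, about 1 point more than always using t. Reporting the smaller of the two p-values gives 56%, 48%, 38% and 29%, which is 3 to 7 points more.

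**Step 5: precision of the alternative.** The half-width of a 95% confidence interval for a mean paired change, in units of the SD of change, is t(0.975, n − 1)/√n.

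- n = 30: 2.045/√30 = 0.37
- n = 35: 2.032/√35 = 0.34

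**The case against.** The other side has a good case on several points.

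- **These outcomes decide nothing.** They are secondary and exploratory, and every success criterion lies elsewhere. A reader might infer that a significant change will be presented as efficacy, but the article nowhere says so. This stands, and it sets the severity.
- **The tests are not the only analysis.** A reader might take the plan to be p-values alone. It is not: descriptive statistics for each measure are promised in the same paragraph, and a paired t test is itself computed from the mean change and its SD. This also stands. However, descriptives of each measure do not commit the authors to reporting the SD of the paired change or the correlation.
- **The test is not said to be chosen from the data.** The Wilcoxon alternative invites that reading, but no selection rule is given, and Step 4 shows that a normality pre-test would hardly matter. Only taking the smaller p-value would, and nothing suggests that is intended.
- **One in two is close to the ceiling for the 13 named scales.** It requires independent scales, and scales answered by the same patients are likely to be correlated. Hence the range.
- **Low power is a weak complaint.** No power is claimed for these scales. With 30 pairs, 80% power needs a standardised change of 0.53, but power at 0.5 is already 75%, and it is 82% with 35 pairs.
- **Confidence intervals cure neither problem by themselves.** Thirteen unadjusted 95% intervals exclude zero as often as thirteen t tests reject, and they carry the same bias from having no control. This is correct. The gain comes from describing the results as change and from not reading the intervals as tests.
- **Alpha, multiplicity rules and intervals may sit in a full protocol or analysis plan that is not shown.** Their absence is therefore not counted here. The point rests on the testing that the article does commit to.

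**Conclusion.** The point holds as a low-severity mismatch between analysis and design. Significance testing of at least 13 scales, in one uncontrolled group of at most 35 that was not sized for testing, has roughly a 25–50% chance of at least one significant result when nothing has changed. The lower end corresponds to a correlation of 0.7 and the upper end to independence. If 17 scales were tested, the independent figure would be 58%. Even the lowest simulated value, 26%, is about five times the nominal 5% (0.26/0.05 = 5.2).

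These figures rest on an assumed two-sided 5% per test, about 30 pairs, and normal, equally correlated change scores. Separately from the figures, no change on any scale, however significant, can be credited to the intervention.

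The feasibility and acceptability conclusions are unaffected.

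**What to change.** In the Quantitative data section, replace the sentence on paired testing with a descriptive plan. For each QLQ-C30 and HADS scale, report:

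- the mean paired change from baseline to week 8 with its 95% confidence interval, using a bootstrap interval if the changes are skewed;
- the SD of the change;
- the baseline/week-8 correlation;
- the number of pairs.

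State that these results are descriptive, that they are reported as change rather than effect, that the intervals will not be read for whether they exclude zero, and that no efficacy statement will be drawn from them. If the authors want to keep one test, they should name one scale and one test in advance.

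The cost is a few lines of wording and the loss of the p-values. No extra data, visits or participants are needed. In return, the planned comparative study gets figures it can use for sizing, with an expected interval half-width of about 0.37 SD of change from 30 pairs.

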##### Qualitative data

Qualitative data will be obtained via two modalities. Firstly, open-ended questions will be provided in the satisfaction survey at the end of week 8 to elicit qualitative feedback. Any qualitative feedback provided will be exported to a single software for thematic analysis. Secondly, following the completion of the programme, 15 interviews will be conducted and will continue if not saturated. Interviews aim to expand on the quantitative satisfaction questions by exploring prior or current barriers to physical activity and the potential impact (e.g. behaviour and attitude change), usability, and friendliness of ExerciseGuide UK.

All interviews will be transcribed verbatim and analysed using thematic analysis. Using inductive coding, transcriptions will be interpreted, and codes will be generated. The strength of convergence of generated themes will be examined based on the overlapping frequency and range.

##### Sample size

Given that this study is a feasibility study with pre-established criteria for success instead of a primary outcome assessment, a formal sample size calculation is not necessary [46]. The sample size for this study is a maximum of 35 individuals LWBLC. The sample size was based on the previous research into online supportive care for those LWBLC and clinician expertise. Firstly, previous research exploring online supportive care for those LWBLC was considered. A recent review reported a mean sample size of eight studies examining online supportive care for those LWBLC [40]. Of the eight studies, six were pilot and feasibility studies. The mean sample size over the six pilot and feasibility studies was 29 ± 33, which demonstrated satisfactory detection of feasibility and acceptability concerns. Furthermore, literature highlighted 35 participants is satisfactory per group [78]. Secondly, clinical expertise was sought out. Based on the recommendation from a senior academic lung cancer clinician based on the studies specified recruitment period (5 months) based on multiple considerations (e.g. caseload and eligibility criteria). Furthermore, the sample of 35 individuals consulted with statistician regarding to ensure adequate size to determine feasibility issues.

## Discussion

The primary aim of this study is to explore the feasibility and acceptability of ExerciseGuide UK (an online supportive care platform) for those LWBLC. In addition, the publication of the protocol aims to increase the transparency and reliability of the study and methods.

Online supportive care has been a rapidly emerging field in exercise oncology over the past decade, especially since the inception of COVID-19 in March 2020. However, a recent review exploring the feasibility of exercise interventions delivered via telehealth for those living with and beyond cancer [31] highlighted a lack of research for those LWBLC. For example, of the 29 interventions Morrison and colleagues (2020) appraised, 6.9% of interventions were within those specifically LWBLC. Furthermore, no study explored exercise and telehealth for those LWBLC within the UK [31]. Data collected through the International Cancer Benchmarking Partnership has shown that over the past several decades, in countries with similar healthcare systems (Australia, Norway, Canada, Denmark, New Zealand, Ireland, and the UK), the UK has ranked lowest for 1-year lung cancer survival [79]. Thus, highlighting further research is paramount to address the below-average survival rate for those LWBLC.

ExerciseGuide UK provides a unique and novel method of providing those LWBLC with an 8-week tailored physical activity programme and personalised educational resources using distance-based methods. Supervised (in-person) exercise interventions are thought to be superior to unsupervised exercise programmes [29]. However, ExerciseGuide UK provides non-real-time supervision while using a distance-based approach. Though, there is limited existing high-quality evidence for those LWBLC. Those LWBLC often display a higher unmet symptom burden and lower quality of life than other prevalent cancer types [80]. Higher unmet symptom burdens and lower quality of life may lead to physical, psychological, and financial disparities, leading to unattainable or achievable standard in-person exercise programmes. Literature has demonstrated key benefits of digital technology regarding accessibility, reach, and convenience through online or computer-mediated communication because it can mitigate temporal and geographical barriers [81–83]. ExerciseGuide UK can maintain personally tailored content for those restricted by location or schedule.

Though ExerciseGuide UK presents possible benefits for those LWBLC, there are some noted limitations. Firstly, while digital technology can reduce temporal and geographical barriers to interventions, this is dependent on several presumptions. Having access to a laptop, computer, or smart device (e.g. tablets and smartwatches) that would enable participation may be varied. Lung cancer incidence is higher for those living in deprived regions and with lower socioeconomic status [84]. However, reports illustrate that those living in urban areas have higher-speed Internet availability [85] compared to those living in rural. Overall, urban areas tend to be more socially deprived than rural areas [86]. Furthermore, the average cost of fixed data (broadband) and voice packaged monthly costs in the UK was £37.25 [87].

Secondly, research waste is an ongoing concern within health research. Up to 85% of research within health is understood to be wasted due to poor research design, inadequate reviews of literature, and unpublished research [88]. The meaningful involvement of the target population of an intervention may reduce the ongoing concern of research waste [89] while ensuring the intervention is appropriate and meaningful for end-users. ExerciseGuide UK has been adapted using an iterative approach with those LWBLC and their family members and qualitative interviews.

Lastly, recruiting those LWBLC into clinical research can be challenging [90]. The recruitment will occur in a lung cancer clinic with assistance from hospital oncologists.

## Conclusion

ExerciseGuide UK provides a unique and novel approach to providing tailored physical activity programmes and educational resources to those LWBLC. However, there is limited high-level evidence within online supportive care for those LWBLC. Thus, the feasibility study exploring ExerciseGuide UK will provide insight into usability concerns that may be revised prior to larger-scale trials, potentially reducing research waste [91]. Building on the evidence collected as part of the feasibility and acceptability trial, the authors plan to revise the website and explore methods of facilitating digital technology usage within lung cancer, comparative assessment of those using a digital physical activity tool vs standard care, and further development of physical activity and health advice (e.g. nutrition).

## Data Availability

Not applicable

## Abbreviations

LWBLC: Living with and beyond lung cancer
PHP: Hypertext pre-processor
ACSM: American College of Sports Medicine
COVID-19: Coronavirus 19
RCT: Randomised control trail
PPI: Patient and public involvement
SMART Goals: Specific, Measurable, Attainable, Realistic, and Timely Goals
EORTC: European Organisation for Research and Treatment Of Cancer
SPIRIT: Standard Protocol Items: Recommendations for Interventional Trials
